## Abstract

**Background:**

Colorectal cancer (CRC) is the second most prevalent type of cancer in Europe. Early detection and removal of CRC or its precursor lesions by population screening can reduce mortality. Colonoscopy and computed tomography colonography (CT colonography) are highly accurate exams and screening options that examine the entire colon. The success of screening depends on the participation rate. We designed a randomized trial to compare the uptake, yield and costs of direct colonoscopy population screening, using either a telephone consultation or a consultation at the outpatient clinic, versus CT colonography first, with colonoscopy in CT colonography positives.

**Methods and design:**

7,500 persons between 50 and 75 years will be randomly selected from the electronic database of the municipal administration registration and will receive an invitation to participate in either CT colonography (2,500 persons) or colonoscopy (5,000 persons) screening. Those invited for colonoscopy screening will be randomized to a prior consultation either by telephone or a visit at the outpatient clinic. All CT colonography invitees will have a prior consultation by telephone. Invitees are instructed to consult their general practitioner and not to participate in screening if they have symptoms suggestive for CRC. After providing informed consent, participants will be scheduled for the screening procedure. The primary outcome measure of this study is the participation rate. Secondary outcomes are the diagnostic yield, the expected and perceived burden of the screening test, level of informed choice and cost-effectiveness of both screening methods.

**Discussion:**

This study will provide further evidence to enable decision making in population screening for colorectal cancer.

**Trial registration:**

Dutch trial register: NTR1829

## Background

Colorectal cancer (CRC) is the second most prevalent type of cancer in Europe. In 2006, 412,900 persons were diagnosed with CRC and 207,400 persons died from the disease[1]. In the Netherlands, more than 4,700 persons died as a result of CRC in 2006[2,3]. The prognosis of patients with CRC depends on the clinical and pathological stage at the time of diagnosis. Early detection of CRC reduces CRC-related mortality; early detection and removal of its precursor lesions -adenomas- reduces both the incidence and mortality of CRC[4]. Thus, population screening of asymptomatic average risk persons can reduce the mortality rate [5-8]. In addition, given the high, rapidly rising costs of treatment of CRC, screening has actually become cost saving[9].

The currently available options for colorectal cancer screening are stool based tests (guaiac and immunochemical faecal occult blood tests and faecal DNA tests) and structural exams (flexible sigmoidoscopy, colonoscopy, double contrast barium enema and CT colonography). Colon capsule is another technique that examines the entire colon. However, this modality is currently not accepted for CRC screening[10,11].

Randomized clinical trials evaluated guaiac-based FOBT (gFOBT) screening during a 10-year screening period and showed reduction in CRC-mortality[12]. Immunochemical FOBT (iFOBT) is considered a superior screening test, because of its better reproducibility and acceptance. Detection rates for advanced adenomas and cancer are higher compared to gFOBT[13]. Furthermore, iFOBT screening offers the option to select a cut-off level matching the optimal performance of the test in a given population with the available colonoscopy capacity[14,15]. A new method of CRC screening that tests DNA markers in stool (sDNA) may be a promising tool for screening in the future. At this moment sDNA does not provide any advantages as a screening method compared with FOBT. Flexible sigmoidoscopy (FS) is an endoscopic procedure, in which the distal 40-60 cm of the colon is inspected. Total colonoscopy is advised in case of positive findings. FS has a threefold higher detection rate for advanced neoplasia compared with FOBT[16,17]. Double contrast barium enema (DCBE) and capsule endoscopy can be considered as inferior screening modalities than colonoscopy. Accuracy was considerably lower and these techniques were not tested in an average risk screening population[18,19].

Colonoscopy and CT colonography are structural exams allowing inspection of the entire colon. Colonoscopy is widely accepted as the clinical reference standard for the detection of colorectal neoplasia and has the advantage that removal of adenomas or early cancer can be performed during the same procedure. All other screening procedures require colonoscopy for confirmation of a diagnosis and, if applicable, therapy (polypectomy) in case of a positive test result. Furthermore, colonoscopy screening can be performed with long intervals since the risk of developing CRC after a negative colonoscopy remains decreased for more than 10 years[20,21]. Despite the excellent sensitivity and specificity of colonoscopy, miss rates of 2.1% for large adenomas (≥ 10 mm) are reported in tandem colonoscopy studies[22]. A disadvantage of colonoscopy as a screening method is its complication rate of 0.1 to 0.3% including post polypectomy bleeding and perforation [23-25]. Secondly, colonoscopy is a burdensome procedure for which full bowel cleansing is necessary. These factors together explain the limited uptake of colonoscopy as a primary screening test and the insufficient use of colonoscopy for surveillance after previous adenoma removal[26]. Finally, colonoscopy capacity is a limiting factor for its widespread use as primary screening test.

CT colonography is a less invasive full colonic exam which can be performed with limited bowel preparation and could therefore be a good alternative in a screening setting [27-29]. CT colonography has been demonstrated to have a high sensitivity for the detection of CRC (96%)[30]. A large screening trial evaluating CT colonography and same day colonoscopy studied 1233 asymptomatic individuals and reported high sensitivity (94%) and specificity (96%) per patient for large adenomas (≥10 mm). Sensitivity and specificity for adenomas larger than or equal to 6 mm was 89% and 80% respectively[31]. The diagnostic yield for advanced neoplasia of CT colonography (3.2%) was comparable to that of colonoscopy (3.4%)[32]. The risk of complications is extremely low, there were no perforations or other serious complications in a large CT colonography screening cohort[32]. CT colonography with limited bowel preparation has a lower burden and is preferred by patients compared to regular CT colonography[33]. A disadvantage of CT colonography is the exposure of individuals to ionizing radiation. However, the chances of radiation induced malignancy are considered very low, especially when a low dose protocol is used. The detection of extracolonic findings in CT colonography could be beneficial, but risks and costs associated with false positives and inconsequential findings may be substantial. Of all available screening tests for CRC, colonoscopy and CT colonography are the most accurate exams.

The optimal screening test for CRC is still a subject of fierce debate. FOBT and FS are suboptimal tests whereas full colonic exams, such as colonoscopy and CT colonography are associated with risks, costs and high workload. An evidence-based estimate of the participation rate is essential for making predictions of the effectiveness and costs of a population screening programme.

In the Netherlands, population based screening trials by gFOBT, iFOBT and FS have already been performed. Studies that investigated stool-based tests as a screening method reported participation rates of 47-50% (gFOBT) and 60-62% (iFOBT)[13,17]. FS-screening had a lower participation rate of 32%[17].

We will conduct a study evaluating the participation rate of both colonoscopy and CT colonography as a screening method in a population-based programme. Since colonoscopy is a more invasive procedure, participation in a colonoscopy screening programme can be expected to be lower than in FOBT and FS screening[34]. On the other hand, FOBT and FS screening should be repeated every 2 and 5 years and participation over a 10 years period could be considerably lower than for a single round of screening[6]. Participation rates might be influenced by the burden of the screening procedure itself and its bowel preparation. We will therefore evaluate the expected and actual perceived burden of both screening methods, as well as the reasons to participate or not in the screening programme.

In most settings, all patients planned for colonoscopy are invited for a prior consultation at the outpatient clinic. In an effort to reduce the number of patients not attending for colonoscopy, *Rodger J et al. *introduced a consultation by telephone in a FOBT positive population in a CRC screening programme and found a significant reduction of 14.1%[35]. Therefore, we hypothesize that a consultation by telephone instead of an appointment at the outpatient clinic prior to colonoscopy could contribute to a higher participation rate in primary colonoscopy screening. Screening invitees should be enabled to make a well-informed decision to participate or not and we will evaluate the level of informed choice in the decision making process[36,37]. Since the expected costs and workload of a population based screening programme by colonoscopy and CT colonography are serious concerns, we will evaluate the cost-effectiveness and feasibility and compare these with the other available screening techniques in the Netherlands.

## Methods and design

### Objectives

#### Primary objective

To compare the participation rates in a population-based screening programme for colorectal cancer by primary colonoscopy and CT colonography.

#### Secondary objectives

• To compare the diagnostic yield of both screening techniques (detection rates of cancer, advanced adenomas and adenomas).

• To compare the expected and perceived burden of colonoscopy and CT colonography.

• To compare the cost-effectiveness and feasibility of colonoscopy and CT colonography as screening methods.

• To compare the level of informed choice in the decision-making process for (non-) participation in colonoscopy and CT colonography screening.

### Study design

This study will be a two-centre randomized controlled trial. A cohort of 7,500 persons of the Amsterdam and Rijnmond region will be randomly selected from the electronic database of the regional municipal administration registrations (Gemeentelijke Basis Administratie (GBA)). In total, 2,500 persons will be randomly selected to receive an invitation for colonoscopy screening with a prior consultation by telephone. Another 2,500 persons will be randomly selected to receive an invitation for colonoscopy screening with a prior consultation at the outpatient clinic. A third group of 2,500 persons will be randomly selected to receive an invitation for CT colonography, with a prior consultation by telephone [figure 1]. Randomization will be performed per household, stratified for age, sex and socio-economic status (SES).

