### Data analysis

We will calculate the participation rate as the number of participants undergoing the screening test relative to the total number of all eligible invitees. We will compare the participation rate between the three screening programmes, and express it as relative participation rates, calculating corresponding 95% confidence intervals, using colonoscopy screening with a prior consultation at the outpatient clinic as the reference strategy.

We will test the null hypothesis of no difference in participation rate using chi-square test statistics. We will also calculate a conditional relative participation rate using logistic regression modelling, accounting for baseline variables. If the overall hypothesis of no difference is rejected, we will test the null hypothesis of a difference in mode of invitation to direct colonoscopy. Additionally, we will test the null hypothesis of no difference in participation between CT colonography screening and direct colonoscopy screening.

The detection rate of the screening test is defined as the proportion of screenees with detected advanced neoplasia. Advanced neoplasia comprises all carcinomas and advanced adenomas together. An advanced adenoma is defined as an adenoma ≥ 10 mm, with villous histology (≥25% villous) or with high grade dysplasia. The most advanced detected lesion per screenee will be used to calculate the detection rate.

The diagnostic yield per 100 invitees is defined as the proportion of screenees with detected advanced neoplasia relative to all eligible invitees.

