### Sample size

We anticipate a participation rate of 22.5% in colonoscopy screening with a prior consultation at the screening centre, a participation rate of 27.5% with prior consultation by telephone, and a participation rate of 35% in the CT colonography group (based on the participation rate of FS screening in the Netherlands)[17]. Including 7,500 participants in the trial will then achieve a power exceeding 99% to reject the null hypothesis of no difference, using a 2 degrees of freedom Chi-Square test with a significance level set at 0.05.

These numbers will lead to a 98% power to reject subsequently the hypothesis of no difference in participation for the two consultation modes with direct colonoscopy, and a power exceeding 99% for the two other pair wise comparisons between screening programmes.

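### Randomisation is per household, but the primary chi-square test, its confidence intervals and the stated power treat invitees as independent

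*Protocol article*

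**What the plan says.** The Study design section fixes the unit of allocation: "Randomization will be performed per household, stratified for age, sex and socio-economic status (SES"). The same section samples and counts persons, for example "A third group of 2,500 persons will be randomly selected to receive an invitation for CT colonography". Households are not mentioned again.

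The Data analysis section defines participation per eligible invitee and names the test: "We will test the null hypothesis of no difference in participation rate using chi-square test statistics". It adds 95% confidence intervals for relative participation and a logistic model with baseline variables. No household term, robust variance or other allowance for clustering is named. The pairwise tests follow only if the overall test rejects.

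The Sample size section gives the overall power as "Including 7,500 participants in the trial will then achieve a power exceeding 99% to reject the null hypothesis of no difference". The calculation behind that figure was made with an ordinary test on 2 degrees of freedom at the 0.05 level. For the consultation-mode contrast it assumes 22.5% with a clinic visit and "a participation rate of 27.5% with prior consultation by telephone", and continues: "These numbers will lead to a 98% power to reject subsequently the hypothesis of no difference in participation for the two consultation modes". No household size, correlation or inflation factor appears.

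**The concern.** Per-household allocation is needed only to keep housemates in the same arm, so the design itself presupposes that some households contribute more than one invitee. Housemates then receive the same leaflet, the same test offer and the same consultation mode, and positive correlation in whether they attend is plausible. If it is present, an ordinary chi-square test uses too small a variance. The p-value of the primary test and every interval for relative participation would look more precise than they are.

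The contrast most exposed is telephone against clinic consultation, because its anticipated difference of 5 percentage points is the smallest of the three.

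**Working it through.** **Inputs from the protocol article.** 2,500 invitees per arm; anticipated participation of 22.5% (clinic), 27.5% (telephone) and 35% (CT colonography); significance level 0.05; stated power 98% for clinic against telephone and above 99% for the rest.

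**Step 1: reproduce the stated power with independent persons.** Pooled rate 0.25.
- SE under the null = √(0.25 × 0.75 × 2/2,500) = 0.01225.
- SE under the alternative = √((0.225 × 0.775 + 0.275 × 0.725)/2,500) = 0.01223.
- Power = Φ((0.05 − 1.96 × 0.01225)/0.01223) = Φ(2.13) = 98.3%.

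The other stated powers also reproduce: above 99.9% for the 2-df test (noncentrality 97.5), for CT colonography against clinic, and for CT colonography against telephone. The 98% therefore contains no allowance for clustering.

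**Step 2: design effect.** Let f be the share of invitees who have one co-invited housemate and ρ the within-household correlation of participation. Assume at most two invitees per household and the same f and ρ in each arm. The variance per invitee is then p(1 − p)[(1 − f) + f(1 + ρ)], so DE = 1 + fρ. **Neither f nor ρ is in the document; both are assumptions.** Examples: f = 0.2, ρ = 0.1 gives 1.02; f = 0.2, ρ = 0.5 gives 1.1; f = 0.4, 0.6 or 0.8 with ρ = 0.5 gives 1.2, 1.3 or 1.4.

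**Step 3: consequences.**
- True size of the uncorrected 2-df test: P(χ²₂ > 5.991/DE) = 0.05^(1/DE).
- True size of an uncorrected pairwise test, ignoring the gate: 2 × [1 − Φ(1.96/√DE)].
- Factor by which intervals should be wider: √DE.
- Power of a correctly sized consultation-mode test: Step 1 with both standard errors multiplied by √DE.

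| DE | 2-df type I error | Pairwise type I error, ungated | CI width factor | Power, 22.5% vs 27.5% |
|---|---|---|---|---|
| 1.00 | 5.0% | 5.0% | 1.00 | 98.3% |
| 1.02 | 5.3% | 5.2% | 1.01 | 98.2% |
| 1.1 | 6.6% | 6.2% | 1.05 | 97.4% |
| 1.2 | 8.2% | 7.4% | 1.10 | 96.2% |
| 1.3 | 10.0% | 8.6% | 1.14 | 94.8% |
| 1.4 | 11.8% | 9.8% | 1.18 | 93.2% |

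A simulation of paired and single invitees (20,000 runs, f = 0.6, ρ = 0.5, so DE 1.3) agrees: under the null, the uncorrected 2-df test rejected in about 9.9% of runs and the ungated pairwise test in 8.6%.

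**Step 4: the bound.** With at most two invitees per household, DE cannot exceed 2.0 (f = ρ = 1). There, consultation-mode power is 82.3%, CT colonography against telephone 98.2%, and CT colonography against clinic and the 2-df test are both above 99.9%.

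**The case against.** The best counter-argument is that the harm is conditional. The article says that persons are drawn at random from a municipal register; it does not say that whole households are invited. If sampling was individual and the register large, co-invited housemates could be few, and per-household allocation would only keep those few together. At DE 1.02 the overall test has a size of 5.3%, which is negligible. This stands: the document shows that f is above zero, not that it is large. It does not remove the mismatch between the allocation unit and the named analysis.

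The gate also matters. If all three arms truly have equal participation, a pairwise test is reached only after the overall test rejects. In the same simulation the gated pairwise error was about 5.1%, against 2.4% under independence. The ungated column therefore applies to the consultation-mode contrast when CT colonography truly differs, which is what the anticipated rates imply; the gate then opens almost always. The gate does not protect the overall test. Stratified allocation makes an unadjusted test slightly conservative and offsets a little, by an amount that the document does not allow one to compute.

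One could also say that the choice of variance estimator belongs in an analysis plan that is not shown, and that a chi-square statistic might be a design-corrected one. But the article itself fixes the allocation unit, the test and a power figure that holds only under independence.

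A reader might further infer that a household cannot be stratified by age and sex, since these belong to individuals. The text does not support that: strata can be formed from household composition or from an index person, and a condensed article may leave such mechanics to the full protocol.

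**Conclusion.** Wrong as written: the allocation unit does not match the stated test, intervals and power. The direction of the error is clear provided that co-invited housemates' decisions are positively correlated. Its size rests on f and ρ, which the document does not give, and on households of at most two invitees. Over the assumed DE of 1.02 to 1.4, it ranges from trivial to a roughly doubled type I error for the overall test, with intervals 1% to 18% too narrow relative to their present width.

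Two stronger readings are not supported. It cannot be asserted that the type I error materially exceeds 5%; that depends on how many housemates were co-invited. Nor is the trial too small: the overall test and both CT colonography comparisons keep at least 98% power at DE 2.0, and the consultation-mode contrast keeps about 93% or more up to DE 1.4. The weight of the point is on the validity of the p-values and intervals, with power second.

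**What to change.** **Data analysis.** Use household-clustered inference for the primary test, the intervals for relative participation and the logistic model. Either a Rao-Scott corrected chi-square, or GEE or modified Poisson regression with household-robust variance and a 2-df Wald or score test, would do.

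**Sample size.** Restate the consultation-mode power with an explicit assumed design effect and the household share and correlation behind it: about 93% to 97% for DE 1.1 to 1.4. The other power statements need only a note that they withstand clustering.

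**Cost.** Slightly wider intervals and a slightly lower stated power. No more invitees are needed. The analysis file must carry a household identifier; the article does not say whether it does, but allocating per household requires households to be identifiable.

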**Figure 1 F1:**
[figure not shown]
**Design of the screening trial**. Flow chart.

### Study population

Our study population consists of 7,500 individuals between 50 and 75 years of age living in our target areas. The selected areas comprise all SES-categories (very low, low, average, high and very high) and are based on data of Statistics Netherlands[3]. The target areas will not have been selected for previous pilot trials on CRC screening. Individuals with CRC symptoms in the previous three months (rectal blood loss and/or changed bowel habits) are advised in our information leaflet to consult their general practitioner and to not participate in screening. Persons who underwent full colonic examination in the previous 5 years (complete colonoscopy and/or double contrast barium enema) are also instructed not to participate and are excluded from the screening programme, as well as individuals planned for surveillance colonoscopy, because of personal history of colorectal cancer, colonic adenomas or inflammatory bowel disease (IBD)). Persons with a severe or terminal disease with a life-expectancy of less than 5 years are excluded. Although pregnancy is not likely in this cohort, pregnant women are also excluded. For CT colonography, individuals exposed to ionizing radiation for research purposes within the previous 12 months and individuals with hyperthyroidism are excluded.

### Invitation procedure

Similar to our previous CRC screening trials, a specialized database will be used for the logistics of the invitational procedure. All invitations will be sent out between June 2009 and September 2010 by the regional Comprehensive Cancer Centres in Amsterdam and Rotterdam.

Members of the target population will receive a pre-announcement, followed by an invitation for the screening programme two weeks later, both by mail. Information leaflet and reply card are sent together with the invitation. All invitees have three options to respond: by returning the reply-card, by calling the Comprehensive Cancer Centre or by sending an e-mail. The Comprehensive Cancer Centre will make an appointment for a prior consultation. All non-respondents will receive a reminder by mail 4 weeks after the initial invitation.

